### Primary outcome measurement

The NPQ has been widely used in research and has been shown to have high validity and reliability for neck pain measurement [19, 20]. It comprises nine items on the degree and duration of pain, symptoms including numbness, sleep, social activities, and quality of life. The highest score is 100 and high scores indicate severe damage due to neck pain. The efficacy is measured as the percentage improvement in the NPQ. If the efficacy is greater than 30%, the treatment is considered to be successful. The NPQ efficacy rate is the percentage of participants for whom treatment was successful. It will be assessed using repeated longitudinal analysis per group.

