### Sample size calculation

The expected efficacy rate of the *tuina* group measured by the NPQ is 95%. According to the literature, the efficacy rate for traditional Chinese massage is 85%. The sample size was calculated with a significance level of 0.05 and power of 0.80. According to the calculation in SPSS, the required sample size was 320. With a maximum dropout tolerance of 10%, 356 patients are needed for the trial, with 178 for each group across the four centers.

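### The primary NPQ endpoint is cut to success or failure where 85–95% are expected to succeed, while the Abstract and analysis section point to the score; naming the score as primary would be less fragile

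*Protocol article*

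**What the plan says.** Primary outcome measurement describes the NPQ as a graded score: "The highest score is 100 and high scores indicate severe damage due to neck pain". It defines efficacy as percentage improvement, then dichotomises it: "If the efficacy is greater than 30%, the treatment is considered to be successful". The result is summarised as a proportion: "The NPQ efficacy rate is the percentage of participants for whom treatment was successful".

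Sample size calculation uses that proportion. For tuina, "The expected efficacy rate of the *tuina* group measured by the NPQ is 95" per cent; for the comparator, "According to the literature, the efficacy rate for traditional Chinese massage is 85" per cent. It continues: "The sample size was calculated with a significance level of 0.05 and power of 0.80", and "According to the calculation in SPSS, the required sample size was 320". A 10% dropout allowance brings this to 356, or 178 per arm.

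Other sections read differently. The Abstract gives the primary outcome as changes in the NPQ, with no threshold, analysed by repeated measures ANOVA. Statistical analyses plans the same ANOVA for efficacy, with treatment, time and interaction terms. That method suits scores, not a yes/no outcome. Outcome measurements names the NPQ itself as the primary measure and mentions no cut.

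**The concern.** Both arms receive active massage, and the question is whether tuina is the better one. On the protocol's own planning rates about 90% of patients pass the 30% threshold. A patient who improves by 35% then counts the same as one who improves by 95%, and all the information comes from the few who fail.

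If the success rate is the primary comparison, two things follow. More patients are needed than the NPQ scores might require. The result also becomes sensitive to modest errors in the planning rates: a control rate a few points higher, or a gain a few points smaller, sharply reduces the chance of detecting a real difference. If the score is primary, as the Abstract suggests, the sample size was derived for a different endpoint. Either way, the reader cannot tell which NPQ result will decide the trial.

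**Working it through.** **Inputs.** Success rates 0.95 and 0.85, significance level 0.05, power 0.80, 320 patients before dropout, 10% dropout (all from Sample size calculation); 1:1 allocation (Abstract, Study design). The sample-size section does not state sidedness; two-sided is the variant that reproduces the figure.

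**1. The plan's own figure.** Mean rate p = 0.90.
- Uncorrected n per arm = [1.960·√(2·0.90·0.10) + 0.842·√(0.95·0.05 + 0.85·0.15)]² / 0.10² = 140.1.
- Continuity-corrected n = (140.1/4)·[1 + √(1 + 4/(140.1·0.10))]² = 159.5, so 160 per arm and 320 in total.
- 320/0.90 = 355.6, so 356.

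Both stated figures reproduce, which confirms that the trial was sized on the success rate.

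**2. Events.** Expected failures are 0.15·160 = 24 in control and 0.05·160 = 8 in tuina: 32 of 320.

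**3. Power of the success rate at 160 per arm.** Exact binomial enumeration gives 0.816 with the continuity-corrected test, 0.824 with Fisher's test and 0.868 with the uncorrected chi-squared test. The continuity-corrected formula gives 0.801. All meet the stated 0.80.

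**4. Power of the full scale, by assumption.** The article gives no NPQ mean or SD. Assume that percentage improvement is normal with the same SD in both arms. The two rates then imply a standardised difference of z(0.95) − z(0.85) = 1.645 − 1.036 = 0.608. A two-sided t test at 160 per arm has power 0.9997, and 44 per arm would give 0.80. The gain is 0.9997 − 0.868 = 0.13 at the low end and 0.9997 − 0.801 = 0.20 at the high end.

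**5. How far that depends on the assumption.**
- *Shape matters little.* Beta-distributed improvement gives a standardised difference of 0.60–0.63, and capping improvement at 100% gives 0.56–0.61. Power stays above 0.998.
- *Spread matters a great deal.* Let r be the ratio of tuina SD to control SD, with the 95% and 85% rates held fixed. The standardised difference is (1.645r − 1.036)/√((1 + r²)/2):

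| r | Standardised difference | Power, 160 per arm |
|---|---|---|
| 1.0 | 0.608 | >0.999 |
| 0.9 | 0.467 | 0.99 |
| 0.85 | 0.390 | 0.94 |
| 0.8 | 0.309 | 0.79 |
| 0.75 | 0.223 | 0.51 |
| 0.7 | 0.133 | 0.22 |

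- *Tail-only effect.* If tuina only rescues would-be non-responders and leaves everyone else unchanged, simulated full-scale power is 0.33 (Wilcoxon) to 0.40 (t test).

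**6. Fragility to the planning rates.** At 160 per arm, with the equal-SD assumption for the score:

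| Tuina vs control | Success rate, exact (corrected to uncorrected) | Score, t test |
|---|---|---|
| 95% vs 88% | 0.54–0.62 | 0.99 |
| 92% vs 85% | 0.43–0.51 | 0.91 |
| 95% vs 90% | 0.32–0.39 | 0.90 |

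**The case against.** Three stronger readings are tempting, and the document supports none of them.

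*The trial is underpowered.* It is not. On its own rates the responder comparison reaches the stated 0.80 with any of the usual tests.

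*A fixed 13–20 points of power are lost.* That figure needs near-equal SDs, which the article does not give. It does not suggest unequal spread or a tail-only effect either, but it cannot exclude them, and with enough reduction in spread the score does worse than the rate.

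*The dichotomy is certainly the primary analysis.* The Abstract and Statistical analyses point to the score and to ANOVA. The closing sentence of Primary outcome measurement, on longitudinal analysis, nearly repeats the one used for the continuous secondary scales and could refer to the NPQ or to the rate. If the score governs, no power is lost, and what remains is a sample size derived for another endpoint.

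It is also fair to say that a responder rate is easy to interpret, and that a condensed article need not justify its 30% threshold. A smaller true effect also hurts a comparison of means: at half the implied shift, its power is 0.77.

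These points remove any fixed loss figure. They do not remove the problem, because the section that defines the primary outcome and the section that sets the sample size both rest on the rate. The competing passages also show that a score-based analysis is already among the sponsor's intended methods.

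**Conclusion.** The concern holds in a qualified form. The protocol defines and sizes its primary NPQ endpoint as a success rate near the ceiling, with about 32 informative failures in 320 patients, and elsewhere describes the primary outcome as change in the score.

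The cost is efficiency and fragility, not failure to meet the stated power. Under an equal-SD shift the score would gain about 13–20 percentage points of power, or need about 44 instead of 160 patients per arm. The gain is still about 12–19 points at an SD ratio of 0.9 (0.987 against 0.868 and 0.801). It is gone at about 0.8 or below, and also under a tail-only effect. These figures are for percentage improvement; applying them to a baseline-adjusted score is a further approximation. The change is worth making, but it does not rest on a guaranteed gain.

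**What to change.** - **Primary outcome measurement:** name one primary endpoint, the NPQ score at one stated visit. Compare arms by ANCOVA, or by a mixed model across visits, with baseline NPQ as covariate, and report the adjusted mean difference with its 95% CI. Keep the more-than-30% success rate as a secondary endpoint, tested by chi-squared.
- **Statistical analyses:** align the wording with that endpoint, so that it agrees with the Abstract.
- **Sample size calculation:** leave 320 and 356 unchanged and say that they were derived from the success rate. Quote any power for the score only together with its SD assumption and the range above.

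The cost is amendment wording, with no extra data, visits or patients. The headline result becomes a mean difference instead of a success rate, a small loss of immediacy that the secondary endpoint covers. The amendment must be made before unblinding.

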### Participants and recruitment

Eligible participants are patients diagnosed with CNP according to the clinical guideline for traditional Chinese medicine (Criteria of Diagnosis and Therapeutic Effect of Diseases and Syndromes in Traditional Chinese Medicine, ZY/T001.1–94). Patients whose neck pain has persisted without relief for over 2 weeks such that it impairs their daily activities at work or elsewhere will be informed of this trial. If a patient expresses interest, a clinical trial communicator will describe the trial to them and ask whether they would like to join it. If the answer is yes, a face-to-face interview will be conducted in the reception room for clinical research subjects in the four hospitals. Patients who meet the inclusion criteria and do not meet the exclusion criteria can join once they sign the consent form.

We publicized the trial to potential participants in four ways: 1) by approaching patients with neck pain admitted to an outpatient department or inpatient ward in each center, 2) recruitment posters at each center and nearby community centers, 3) the official microblog and WeChat platforms of each center, and 4) printed adverts in newspapers.

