### Outcome measurements

Four well-recognized self-report tools will be used to measure the outcomes. The Northwick Park Neck Pain Questionnaire (NPQ) will be used as the primary outcome measure. A VAS, Neck Disability Index (NDI), and Short Form 36 (SF-36) will be used as secondary outcome measures. Neck pain-related dysfunction, pain, and quality of life will be assessed at six time points: screening, baseline (after enrollment), weeks 2 (intervention session), 4 (intervention session), 10 (follow-up session), and 16 (follow-up session). We will measure the study participant’s previous experience of the interventions, their expectations for recovery, and their expectation of the importance of the allocated therapy in their recovery (just after the unmasking and before the intervention starts).

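### NPQ success is a percentage of each patient's own baseline and entry sets no NPQ minimum, so the between-arm success comparison should always adjust for baseline NPQ

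*Protocol article*

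**What the plan says.** All references are to the protocol article.

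- **Endpoint (Primary outcome measurement).** "The efficacy is measured as the percentage improvement in the NPQ", and "If the efficacy is greater than 30%, the treatment is considered to be successful". The success rate follows: "The NPQ efficacy rate is the percentage of participants for whom treatment was successful". No absolute change in points is required. The denominator is not spelled out; the natural reading is the patient's own baseline.
- **Scale (same section).** "The highest score is 100 and high scores indicate severe damage due to neck pain". Reliability is described only in words: the NPQ "has been shown to have high validity and reliability for neck pain measurement". No measurement error, reliability coefficient or standard deviation is given.
- **Entry (Inclusion and Exclusion criteria).** Current pain severity is set by a VAS above 3, with conditions on the length, frequency and history of episodes. Neither list has an NPQ minimum. Participants and recruitment adds an unscored functional condition: patients with persistent neck pain "such that it impairs their daily activities at work or elsewhere will be informed of this trial".
- **Analysis (Statistical analyses).** Categorical variables are compared between groups by chi-squared or Fisher's exact test. Covariance analysis is planned only if adjustment for baseline incomparability proves necessary.
- **Size (Sample size calculation).** The trial is sized on NPQ success rates of 95% and 85%.

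**The concern.** A relative rule with no lower limit on the denominator sets a different bar for each patient. At a low baseline the bar is a few points on a 100-point scale, which may lie within ordinary re-test variation. At a baseline of zero the percentage does not exist.

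Two things are at stake. The first is interpretation: a success worth just over 3 points differs from one worth more than 18. The second is precision: if the chance of success depends on baseline NPQ, a comparison that ignores baseline leaves explainable variation in the analysis. Adjusting only when the arms look unbalanced misses this, because the reason to adjust is that baseline predicts the outcome by construction, whether or not the arms differ.

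**Working it through.** **1. The plan's own figure.** Rates 0.95 and 0.85, mean 0.90, two-sided alpha 0.05 (sidedness is not stated), power 0.80:

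n = [1.960·√(2·0.90·0.10) + 0.842·√(0.95·0.05 + 0.85·0.15)]² / 0.10² = (0.832 + 0.352)² / 0.01 = 140.1 per arm.

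With continuity correction: (140.1/4)·[1 + √(1 + 4/(140.1·0.10))]² = 159.5, so 160 per arm and 320 in all. Then 320/0.90 = 355.6, so 356. Both stated figures reproduce. Power at 160 per arm without correction is 0.85.

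**2. The bar in points.** 0.30 × baseline gives 3 at 10, 6 at 20, 9 at 30, 12 at 40 and 18 at 60. Success requires more than this.

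**3. A patient with no true change.** The standard error of measurement (SEM) is not in the article; 3 and 5 points are assumed. If the bar is held at 30% of the true baseline B, P(success) = P(Z > 0.30·B / (√2·SEM)). If the measured baseline is also the denominator, success means 0.7 × measured baseline exceeds follow-up, and √2 becomes √(0.7² + 1) = √1.49.

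| Baseline NPQ | SEM 3: √2 / √1.49 | SEM 5: √2 / √1.49 |
|---|---|---|
| 10 | 24% / 21% | 34% / 31% |
| 20 | 8% / 5% | 20% / 16% |
| 30 | 2% / 1% | 10% / 7% |
| 40 | 0.2% / 0.1% | 4.5% / 2.5% |

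**4. Both arms, all patients at one baseline.** True percentage improvement is taken as normal with SD 15 to 25 percentage points (assumed), centred so that 95% and 85% truly exceed 30%. SEM 3 to 5 is added to both scores. Ranges run over these assumptions, with 160 per arm and no continuity correction.

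| Baseline NPQ | Tuina success | Massage success | Difference (points) | Power |
|---|---|---|---|---|
| 10 | 65–82% | 60–72% | 5.5–10.2 | 17–59% |
| 15 | 72–88% | 64–77% | 7.5–11.0 | 30–74% |
| 20 | 77–91% | 68–80% | 9.0–11.0 | 44–79% |
| 30 | 84–93% | 73–82% | 10.6–11.0 | 63–83% |
| 40 | 88–94% | 77–84% | 10.4–11.0 | 73–84% |

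Success rises with baseline in both arms although the true rates are the same in every row.

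**5. Direction of the errors.** In the same model at baseline 20, false successes are 1.5–2.1% of all tuina patients and 4.1–6.0% of all massage patients; false failures are 5.8–20.5% and 9.3–23.5%. At baseline 40, false successes are 1.1–1.8% and 2.7–4.8%; false failures are 2.2–9.2% and 4.2–13.2%. When most patients truly respond, noise mostly turns responders into failures.

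**6. What adjustment gains.** Baseline NPQ was drawn from a normal distribution with SD 12 (assumed), in 3,000 simulated trials per scenario at true-improvement SD 15 and 25. The unadjusted test was compared with a logistic score test including baseline NPQ. Power moved from 35–62% to 38–65% at mean 20, from 55–79% to 58–80% at mean 30, and from 68–82% to 70–83% at mean 40. The gain was about 0 to 4 percentage points and never negative.

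**The case against.** **The power loss may be counted twice.** The planning rates can be read as rates expected to be observed, with misclassification already in them. Power at 160 per arm is then 0.85 by construction, and the losses in steps 4 and 6 do not apply. This stands: nothing in the article says that 95% and 85% are error-free. A reader might infer that the trial is underpowered, and the article does not support that.

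**Noise is not mainly a source of false success.** A reader might infer that low-baseline patients become successes by noise and that the arms are therefore pulled together. Step 5 shows that false failures dominate. Step 4 shows the difference clearly shrinking only at about 10 to 15; from about 20 to 30 upwards it stays near 10 to 11 points, and power falls because both rates move towards the middle. This stands.

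**Very low baselines may be rare.** A VAS above 3 and impaired daily activities make an NPQ near zero less likely. This stands in part: the VAS asks about pain at the moment of asking, and the functional wording is unscored, so neither guarantees an NPQ value.

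**Averaging screening and baseline scores may not be free.** Outcome measurements has the outcome domains "assessed at six time points: screening, baseline (after enrollment" and so on, but does not name the NPQ at screening. Interventions lists five neck-function assessments starting at baseline, and Statistical analyses counts five efficacy time points. This stands.

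**Covariate choice often sits in the SAP.** That is so where the protocol is silent. Here it sets a rule, adjustment conditional on observed imbalance, which does not suit an endpoint that depends on baseline by definition.

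**Conclusion.** The point holds as a conditional design weakness. It is certain from the text that success is purely relative, that entry sets no NPQ minimum, and that the points required scale with baseline, on the reading that baseline is the denominator. That the chance of success also depends on baseline follows for any non-zero measurement error in the model used.

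The size for this trial is unknown. It rests on the SEM, the baseline distribution and the spread of true improvement, all assumed here. In the favourable scenario (baseline mean 40, SEM 3) simulated power is about 0.80 to 0.82, at the plan's target. In unfavourable ones it is much lower, but only if the planning rates are error-free. The sample size is not shown to be wrong, and an NPQ entry minimum is not shown to be necessary. Baseline adjustment survives because it uses data already collected and was not harmful in any scenario.

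**What to change.** 1. **Statistical analyses.** For the NPQ success comparison, replace adjustment conditional on imbalance with a prespecified between-arm comparison that always includes baseline NPQ as a covariate or stratum, for example logistic regression. Report the adjusted difference in success proportions beside the odds ratio, so that the result can be set against the planned 95% and 85%.
2. **Primary outcome measurement.** State that the denominator is the baseline NPQ and how a baseline of zero is scored.
3. **Sensitivity analysis.** Repeat the comparison in patients whose baseline NPQ is high enough that 30% of it exceeds the scale's measurement error. Give that error, its source and which measure is meant, because the cut-off depends on it. With the SEM itself, 3/0.30 = 10 and 5/0.30 = 16.7. With the 95% smallest detectable change (1.96·√2·SEM, so 8.3 and 13.9 points), the cut-offs are 27.7 and 46.2. The restricted analysis has fewer patients and serves interpretation, not power.

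These are wording changes on data already collected, best made before the database is locked. They leave 320 and 356 unchanged.

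Two further steps are optional. The mean of the screening and baseline NPQ could serve as denominator if the sponsor confirms that the NPQ is taken at screening. An NPQ entry minimum would reduce misclassification, but it narrows the population and, with recruitment under way, would apply only to later patients.

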**Methods/design:**

This is a multicenter, assessor- and analyst-blinded, randomized controlled trial with two parallel arms: a *tuina* group and a traditional Chinese massage group. A total of 356 eligible CNP patients will be randomly assigned to the groups in a 1:1 ratio. The intervention in the *tuina* group includes both structural and relaxation massage, while the traditional Chinese massage group will receive relaxation massage only. The interventions for both groups will last for 15 min and will be carried out three times a week for a period of 4 weeks. The primary outcome will be changes in the Northwick Park Neck Pain Questionnaire. Secondary outcomes will be measured by a visual analogue scale (VAS), the Neck Disability Index (NDI), and the 36-item Short-Form Health Survey (SF-36). The data will be analyzed at the baseline, at the end of the intervention, and during the 3 months of follow-up by repeated measures analysis of variance. The significance level is 5%. The safety of *tuina* and traditional Chinese massage will be evaluated after each treatment session. The results of this trial will help clarify the value of *tuina* and traditional Chinese massage as treatments for CNP and will highlight any differences in the efficacy of the treatments.

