Data normality will be tested through visual inspection of histograms. According to the results of the homogeneity and normality analysis, parametric statistics (Tukey test) or non-parametric statistics (Wilcoxon rank sum test) will be used for the within- and between-group analyses. Descriptive statistics will be used to compare demographic and baseline information and to evaluate the credibility of the groups. If an adjustment for possible baseline incomparability is needed, a covariance analysis will be performed. Efficacy is measured at five time points. Therefore, a repeated measures analysis of variance will be used to investigate the effect of treatment, time, and interaction terms between treatment groups versus time. Two-sided paired *t* tests will use within-group comparisons (comparing baseline to follow-up). A chi-squared test or a Fisher’s exact test will be performed to determine categorical variables between groups and adverse effects, which will be recorded and described as a frequency and percentage. Fisher’s exact test will be used if a cell has an expected value of less than 5 that is equal to or more than 20%. All statistical analyses will be performed with the Statistical Package for Social Sciences (SPSS, version 21.0, SPSS Inc., Chicago, IL, USA) by statisticians who are independent of the research team and blinded to the group allocation. The confidence interval will be established at 95%, and the significance level at 0.05.

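### The 0.80 power belongs to a single between-group comparison of NPQ responder rates, which the plan neither designates as primary nor ties to a visit

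*Protocol article*

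**What the plan says.** Four places in the protocol article bear on the primary analysis.

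- **Abstract, Methods/design:** "The primary outcome will be changes in the Northwick Park Neck Pain Questionnaire". The abstract adds that the data will be analysed by repeated measures ANOVA.
- **Primary outcome measurement:** efficacy is the percentage improvement in NPQ, and a patient with more than 30% counts as a success. Then: "The NPQ efficacy rate is the percentage of participants for whom treatment was successful. It will be assessed using repeated longitudinal analysis per group". No visit is given.
- **Statistical analyses:** efficacy is measured at five time points, and for that reason "a repeated measures analysis of variance will be used to investigate the effect of treatment, time, and interaction terms between treatment groups versus time". The same section provides a chi-squared or Fisher's exact test for categorical variables between groups, without mentioning the NPQ rate. The full analysis set (FAS) is used for the main analysis.
- **Sample size calculation:** the expected tuina rate is 95%, and "the efficacy rate for traditional Chinese massage is 85" per cent. "The sample size was calculated with a significance level of 0.05 and power of 0.80". From this "the required sample size was 320", raised to 356 for 10% dropout.

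The Interventions section lists the assessments as baseline and weeks 2, 4, 10 and 16. The Follow-up section gives both short-term and long-term efficacy as aims, so it does not imply a deciding visit either.

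**The concern.** A power statement holds for one endpoint, one time point and one test. Here the endpoint that was powered is binary and compared once. The analysis named for efficacy is a model over all visits with treatment, time and interaction terms, and the abstract describes the outcome as a change. A reader cannot tell whether the trial succeeds on the responder rate, the treatment term or the treatment-by-time term, nor at which visit.

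Two things are at stake. The 0.80 cannot be claimed for the analysis the article puts forward. And if the deciding endpoint and visit are settled only once results are known, the nominal 5% significance level no longer describes the chance of a false claim.

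**Working it through.** **Inputs.** From Sample size calculation: p1 = 0.95, p2 = 0.85, alpha 0.05, power 0.80, dropout 10%. Allocation is 1:1 (Abstract). Sidedness is not stated for the calculation; two-sided is assumed.

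**Step 1. Reproduce the sample size.** With pooled p = 0.90 and difference 0.10:

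- n = [1.960 × √(2 × 0.90 × 0.10) + 0.842 × √(0.95 × 0.05 + 0.85 × 0.15)]² / 0.10² = 140.1 per arm.
- With continuity correction: n' = (n/4) × [1 + √(1 + 4/(n × 0.10))]² = (140.1/4) × [1 + √1.2855]² = 159.5, so 160 per arm and 320 in total.
- Dropout: 320 / 0.90 = 355.6, so 356.

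Both stated figures are matched exactly. The other variants tried give different totals: two-sided uncorrected 282, two-sided unpooled 276, two-sided arcsine about 266, one-sided continuity-corrected 260, one-sided uncorrected 222. The calculation is therefore an unadjusted comparison of two proportions at a single point.

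**Step 2. Power of that comparison at 160 per arm.**

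| Test | Power |
|---|---|
| Chi-squared, uncorrected, normal approximation | 0.85 |
| Chi-squared, uncorrected, exact enumeration | 0.87 |
| Chi-squared, continuity-corrected, exact enumeration | 0.82 |
| Fisher's exact | 0.82 |

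**Step 3. Power of the named analysis.** A repeated measures ANOVA on NPQ needs a mean difference, an SD and a within-patient correlation. The article gives none of these, so its power cannot be computed from the document.

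**Step 4. Set the sections side by side.**

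| Section | Form of the outcome | Analysis | Deciding visit |
|---|---|---|---|
| Abstract | Change in NPQ | Repeated measures ANOVA | None |
| Primary outcome measurement | Responder rate, more than 30% | Longitudinal, *per group* | None |
| Statistical analyses | Efficacy, five time points | Repeated measures ANOVA | None |
| Sample size calculation | Responder rate, 95% and 85% | Two proportions (Step 1) | None |

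The sample size row agrees with the primary outcome row on the endpoint, but with no row on the analysis.

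**Step 5. Illustrative error rate.** Suppose each of the four post-baseline visits were tested at 5% without correction. With fully correlated visits, the chance of at least one false positive is 5%. With independent visits it is 1 − 0.95⁴ = 0.185. The truth under such a rule would lie between these. The plan does not state such a rule; it only leaves room for one.

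**The case against.** The best defence is that every piece is present. Responder status is a categorical variable, and the Statistical analyses section provides a chi-squared or Fisher's exact test between groups. The ANOVA has treatment and treatment-by-time terms, and the article states a between-group question throughout. The primary outcome section gives one chain, from percentage improvement to success to rate, and an abstract is shorthand.

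Much of this stands, and it rules out several stronger readings that a reader might reach:

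- *The powered hypothesis is never tested.* Not supported. The chi-squared/Fisher provision could cover it. What is missing is any link from that provision to the NPQ rate, a visit or the primary hypothesis.
- *The plan has no between-group test because it says per group.* Not supported. The ANOVA terms compare groups, so those words look like loose drafting.
- *The plan fits an ANOVA to a yes/no outcome.* Not established. Efficacy is defined as the percentage improvement, which is continuous, and the ANOVA can be read as applying to that. For the responder rate no model is named.
- *The type I error is inflated by a known amount.* Not supported. No section plans to pick the best visit or the best form of the outcome. Any single figure would need visit correlations and a selection rule that the document does not give.
- *The continuous analysis is far over- or under-powered.* Not computable. Converting 95% against 85% into a standardised difference requires assuming normality for a percentage that cannot exceed 100, and the plan itself allows for non-normal data.

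The defence does not remove the conflict. A full analysis plan may supply detail, but this article does address the primary endpoint and its analysis, and it does so differently in four places.

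**Conclusion.** The concern holds in this form: the comparison that determined the sample size is not designated as the primary analysis and has no time point, while the efficacy analysis that is named is one for which 0.80 was not calculated and cannot be calculated from the article. The sample size itself is sound and reproduces exactly, assuming a two-sided test with continuity correction.

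Control of the 5% error rate is not guaranteed, rather than shown to be lost. The 5% to 18.5% range is illustrative and assumes uncorrected tests at all four post-baseline visits. This should be corrected because it decides what counts as a positive trial, and the sections conflict rather than merely omit detail.

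**What to change.** Before database lock, state one primary endpoint, visit and test consistently in the Abstract, Primary outcome measurement, Statistical analyses and Sample size calculation:

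- **Endpoint and test:** the proportion with more than 30% NPQ improvement, compared between groups in the FAS by a chi-squared or Fisher's exact test (name one) at two-sided 0.05, with the risk difference and 95% CI.
- **Visit:** one prespecified visit. Week 4, the end of treatment, is an example; the article does not favour any visit, so the sponsor must choose and record it before results are seen.
- **Wording:** in Primary outcome measurement, replace *per group* with *between groups*.
- **Secondary:** the repeated measures ANOVA of NPQ scores, and the responder rates at the other visits.
- **Power statement:** say that 0.80 refers to this unadjusted test at the chosen visit. An analysis adjusted for centre or baseline NPQ can be supportive, but attaching the 0.80 to it would recreate the mismatch.

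The cost is wording only. N stays at 320 evaluable and 356 randomised, and no extra data are needed. The downside is that the other visits and the continuous NPQ can no longer carry the primary claim.
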